## Abstract

**Background:**

Clomiphene citrate (CC) is first line treatment in women with World Health Organization (WHO) type II anovulation and polycystic ovary syndrome (PCOS). Whereas 60% to 85% of these women will ovulate on CC, only about one half will have conceived after six cycles. If women do not conceive, treatment can be continued with gonadotropins or intra-uterine insemination (IUI). At present, it is unclear for how many cycles ovulation induction with CC should be repeated, and when to switch to ovulation induction with gonadotropins and/or IUI.

**Methods/Design:**

We started a multicenter randomised controlled trial in the Netherlands comparing six cycles of CC plus intercourse or six cycles of gonadotrophins plus intercourse or six cycles of CC plus IUI or six cycles of gonadotrophins plus IUI.

Women with WHO type II anovulation who ovulate but did not conceive after six ovulatory cycles of CC with a maximum of 150 mg daily for five days will be included.

Our primary outcome is birth of a healthy child resulting from a pregnancy that was established in the first eight months after randomisation. Secondary outcomes are clinical pregnancy, miscarriage, multiple pregnancy and treatment costs. The analysis will be performed according to the intention to treat principle. Two comparisons will be made, one in which CC is compared to gonadotrophins and one in which the addition of IUI is compared to ovulation induction only. Assuming a live birth rate of 40% after CC, 55% after addition of IUI and 55% after ovulation induction with gonadotrophins, with an alpha of 5% and a power of 80%, we need to recruit 200 women per arm (800 women in total).

An independent Data and Safety Monitoring Committee has criticized the data of the first 150 women and concluded that a sample size re-estimation should be performed after including 320 patients (i.e. 80 per arm).

**Discussion:**

The trial will provide evidence on the most effective, safest and most cost effective treatment in women with WHO type II anovulation who do not conceive after six ovulatory cycles with CC with a maximum of 150 mg daily for five days. This evidence could imply the need for changing our guidelines, which may cause a shift in large practice variation to evidence based primary treatment for these women.

**Trial registration number:**

Netherlands Trial register NTR1449

## Background

There is a lack of evidence on how to best treat women with World Health Organization (WHO) type II anovulation or polycystic ovary syndrome (PCOS) and clomiphene citrate (CC) failure. Women with WHO type II anovulation have absent or irregular ovulation due to hypothalamic-pituitary dysfunction associated with normal levels of endogenous estradiol. The majority of these women can be diagnosed with PCOS. The diagnosis of PCOS is based on at least two of the following three criteria: oligo-ovulation or anovulation, clinical or biochemical evidence of hyperandrogenism, and polycystic ovaries on ultrasound assessment [1].

CC has been used as a first-line ovulation induction agent for over 40 years [2,3]. Systematic reviews and meta-analyses have shown that CC is indeed the best primary treatment option in therapy-naive women with WHO type II anovulation and PCOS [4-8]. Although 60% to 85% of women starting ovulation induction with CC will ovulate, only about one half will have conceived after six cycles [9,10] the so called women with CC-failure.

When anovulatory women ovulate after CC, but do not conceive after six cycles, the clinical problem occurs, that cannot be answered by guidelines. Most trials, randomised or not, have been directed at therapy naïve women, or at women with PCOS that remained anovulatory after CC, also called CC-resistant women [11-18].

For CC-failure, on one hand, women may continue to use CC for another six cycles. On the other hand, they may switch to ovulation induction with gonadotrophins. Both types of ovulation induction may involve intercourse or may be combined with intra-uterine insemination (IUI).

A reason why women should continue CC with regular intercourse is that women do still get pregnant on CC after six treatment cycles, although pregnancy rates per cycle probably drop despite regular ovulation [2,19]. There is consensus that it is best to limit exposure to CC to 12 treatment cycles, as additional cycles may place the woman at increased risk of borderline ovarian tumours [20]. Although it is thus clear that for safety reasons the upper limit of treatment cycles is 12, it is unclear for how many cycles ovulation induction with CC should be repeated from the perspective of effectiveness.

Several studies and one report of an international consensus meeting advise continuation of treatment with gonadotrophins and/or IUI if pregnancy does not occur within six ovulatory cycles [21-24]. This advice is based upon the presumption that lack of conception despite evidence of ovulation may be due to anti-estrogenic effects of CC on the endometrium.

Pregnancy rates with gonadotrophins can be expected to be higher than with CC in women that do not conceive after six ovulatory cycles on CC. The downside is that ovulation induction with gonadotrophins has major disadvantages. It implies daily injections of gonadotrophins combined with concurrent blood and ultrasound monitoring of follicular growth and development. Multifollicular development is not uncommon, despite careful dose adjustment and monitoring, due to the inherent nature of PCOS. Also, injectable gonadotrophins are expensive and the frequent monitoring of follicular growth implies substantial additional cost. Extra costs are generated because treatment cycles often have to be cancelled to minimize the risks of multiple pregnancy and, more rarely, of ovarian hyperstimulation syndrome [25,26].

In IUI motile spermatozoa are concentrated and placed directly into the uterine cavity, in closer proximity to the released oocyt than is the case after vaginal intercourse. There have been no randomised controlled trials that studied the effect of IUI in women undergoing ovulation-induction with CC or gonadotrophins for oligo- or anovulation. Still, IUI is often added to ovulation induction with CC or gonadotrophins. The NICE guidelines actually recommend IUI and prolonged ovulation induction with CC in women who ovulate on CC but do not conceive [27]. IUI is expected to result in higher pregnancy rates than intercourse but requires extra laboratory work and more hospital visits and is therefore much more expensive.

In summary, in women with WHO type II anovulation or PCOS who ovulate on CC but fail to conceive after six ovulatory cycles, prolonged CC or a switch to gonadotrophins, as well as the addition of IUI are treatment options that are often applied in clinical practice. However, data on cost and effectiveness of these options are lacking. We therefore propose to determine which treatment is most cost-effective, thus facilitating a cost-effective and standardised clinical practice in The Netherlands.

## Objective

Our primary objective is to evaluate four treatment regimens in women with WHO type II anovulation that failed to conceive after six ovulatory cycles with CC in terms of singleton live birth. Secondary objectives are to assess the safety and cost-effectiveness for these treatment regimens and to optimise guideline recommendations.

## Methods

### Participating centres

This study is a multicentre randomised controlled trial in The Netherlands and inclusion started in December 2008.

### Inclusion criteria

We will include women with WHO type II anovulation, who have been ovulatory for six cycles on CC treatment, with a maximum of 150 mg daily for five days, but who did not conceive. Ovulation will be assessed by a basal temperature curve, midluteal progesterone (> 16 nmol/l), detection of LH surge or sonography, depending on the local protocol. All women will have at least one patent Fallopian tube, proven by negative Chlamydia antibody titre (CAT), hysterosalpingography (HSG), transvaginal hydrolaparoscopy (THL) or diagnostic laparoscopy combined with tubal testing (DLS and TT), also depending on the local protocol.

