### Study management

All women participating in the study will undergo a basic fertility work-up including a semen-analysis and endocrinological investigation to rule out hyperprolactinemia and uncorrected thyroid dysfunction. Ovulation is induced with CC. From the third or fifth day until the seventh or ninth day after spontaneous or progesterone induced menstruation women will take CC with a minimum of 50 mg to a maximum of 150 mg a day. During the first six treatment cycles women will undergo CAT, HSG, THL and/or DLS and TT to exclude double sided tubal occlusion.

Women are eligible for the study after six ovulatory cycles proven by a cycle length of less than 35 days, a biphasic basal temperature curve, midluteal progesterone (> 16 nmol/l), detection of LH surge or sonography, depending on the local protocol.

Women eligible for the study will be referred to a research nurse for counselling and randomisation.

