**Figure 1 F1:**
[figure not shown]
Flow chart M-OVIN study.

Ovulation induction, semen preparation and insemination regimens will be done according to hospital specific protocols. Ovulation induction with CC will be started on the third to fifth day of a spontaneous menstrual or progesterone induced bleed, in the same dosage as used in the last ovulatory cycle, with a minimum of 50 mg to a maximum of 150 mg daily, for five days. If ovulation does not occur, the dosage will be increased with steps of 50 mg with a maximum of 150 mg daily in the next cycles. As couples are assumed to have regular intercourse, no specific timing advice will be given. Only if couples have a history of sexual problems they are advised to have regular intercourse, at least three times a week. Ovulation will be documented according to local protocol with either a biphasic temperature curve, or a follicle with a diameter ≥16 mm ;on transvaginal ultrasonography. In case of ovulation women will continue taking the same dose of CC until an end point is reached.

Ovulation induction with gonadotrophins will be started at the second to fifth day of a spontaneous or progesterone induced menstrual bleed according to the established chronic low dose step up regimen. Transvaginal ultrasound will be performed on day three of the cycle or according to local protocol. Women will not be stimulated if they have ovarian cysts >25 mm in mean diameter. The starting dose will be 50 or 75 IU daily. The follicular growth is strictly monitored by transvaginal ultrasound. If more than three dominant follicles (≥18  mm) are present, the cycle will be cancelled. When at least one follicle with a diameter of ≥ 16 mm is present, ovulation is induced by the administration of 5000 IU or 10000 IU of human chorionic gonadotrophin (hCG) followed by timed intercourse.

In case of IUI, semen samples will be processed within one hour of ejaculation by density gradient centrifugation followed by washing with culture medium. Women will be inseminated 36 hours after hCG injection. IUI will be performed once per cycle.

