### Outcome measures

#### Primary outcome measure

The main primary outcome measure will be birth of a healthy child resulting from a pregnancy that was established in the first eight months after randomisation. A live birth is defined as any ongoing pregnancy with a gestation time beyond 24 weeks. After randomisation women will receive a maximum of six treatment cycles.

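### Eligibility counts ovulatory CC cycles while the Background's limit of 12 counts treatment cycles, so some women in the CC arms can pass that limit

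*Protocol article*

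**What the plan says.** All references are to the protocol article.

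- **Background.** Citing consensus and a possible risk of borderline ovarian tumours, it says "it is best to limit exposure to CC to 12 treatment cycles". It then treats the matter as settled: "it is thus clear that for safety reasons the upper limit of treatment cycles is 12". The unit is treatment cycles.
- **Inclusion criteria.** Women enter "who have been ovulatory for six cycles on CC treatment, with a maximum of 150 mg daily for five days", without having conceived. The unit is ovulatory cycles.
- **Study management.** The same unit is repeated: "Women are eligible for the study after six ovulatory cycles proven by" one of several local methods. CC before the trial ranges from 50 to 150 mg a day.
- **Exclusion criteria.** CC resistance excludes a woman only if she still does not ovulate at 150 mg. Anovulatory cycles at lower doses do not exclude her.
- **Interventions.** Two of the four arms receive CC for up to six further cycles. During the trial, "If ovulation does not occur, the dosage will be increased with steps of 50 mg", up to 150 mg.
- **Primary outcome measure.** "After randomisation women will receive a maximum of six treatment cycles". The unit is treatment cycles again.

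No section bounds the total of CC cycles before entry, and none shortens the trial course for a woman who has already had more than six.

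**The concern.** The design appears to fit the 12-cycle ceiling because six cycles before entry plus six in the trial make 12. That sum mixes units. The ceiling and the trial course count treatment cycles, whereas the entry rule counts only cycles with ovulation. A cycle in which CC was taken without ovulation is exposure to CC, yet it does not count towards entry.

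The point is one of safety and consistency. If the entry and treatment rules are followed exactly, they permit CC exposure beyond the boundary that the same article calls clear. It arises only in the two CC arms, because the gonadotrophin arms add no CC cycles. It does not touch the power calculation or the analysis.

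**Working it through.** **Inputs**

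- Ceiling: 12 treatment cycles (Background).
- CC cycles before entry that count for eligibility: 6 ovulatory cycles, taken as exactly six (Inclusion criteria, Study management).
- CC cycles in the trial: at most 6 treatment cycles, in two of four arms (Interventions, Primary outcome measure).
- k: earlier CC cycles without ovulation. The document gives neither a value nor a bound.

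**Formula**

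Maximum total CC treatment cycles in a CC arm = 6 + k + 6 = 12 + k.

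**Reproducing the document's figure**

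k = 0: 6 + 0 + 6 = 12. The ceiling is met exactly, with no margin.

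**Other values of k**

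| k | CC cycles before entry | Maximum total | Above 12 | Trial cycle at which the total reaches 12 |
|---|---|---|---|---|
| 0 | 6 | 12 | 0 | 6 |
| 1 | 7 | 13 | 1 | 5 |
| 2 | 8 | 14 | 2 | 4 |
| 3 | 9 | 15 | 3 | 3 |

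The last column is 6 − k. It shows when the count is reached and is not a proposed course length.

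**Where k could come from**

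The 50 mg step rule is written for the trial phase. Suppose the same pattern applied before the trial, with a 50 mg start and one anovulatory cycle per step. Ovulation first achieved at 50, 100 or 150 mg then gives k = 0, 1 or 2. The starting dose and step rule before the trial are not stated, so this mapping is an assumption. The formula does not depend on it: any anovulatory CC cycle before entry, at any dose, adds one.

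**Would women stay in treatment that long?**

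A woman passes 12 only if she starts trial cycle 7 − k. As a rough illustration, take the 40% live birth rate assumed for CC in the Power calculation as the chance of leaving treatment over six cycles, constant per cycle, with no drop-out.

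- k = 1: share starting trial cycle 6 = 0.60^(5/6) = 0.653, about 65%.
- k = 2: share starting trial cycle 5 = 0.60^(4/6) = 0.711, about 71%.

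These shares apply only to CC-arm women who have that k. Drop-out, and pregnancies that do not end in live birth, would change them. They are not a proportion of the trial.

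**What cannot be computed**

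The share of women with k of 1 or more is not given, so no overall number of affected women follows.

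**The case against.** The case on the other side has four parts.

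1. **The limit is not a trial rule.** It stands in the Background as a report of consensus, not as an eligibility criterion or stopping rule, and the Methods sections agree with one another. A reader might infer two conflicting trial rules, but the document does not support that. What stands is that the Background calls the limit clear and gives safety as the reason, and the Methods permit exposure beyond it.

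2. **The wording may be loose.** The article sometimes calls the cycles before the trial simply treatment cycles. If the limit is meant to count ovulatory cycles only, the total is at most 6 + 6 = 12 and nothing is exceeded. This is a fair reading. It is also why the text needs clarifying: as printed, the limit is in treatment cycles and concerns exposure.

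3. **The size can be overread.** A reader might infer that every woman who needed a higher dose will exceed 12. The document does not support this: six is a maximum, treatment ends with a pregnancy leading to birth, the horizon is eight months, and Follow up expects that some couples will not complete it. A reader might also take the whole CC allocation, 2 × 200 = 400 women, as affected. That is the number planned for the two arms, not the number with an earlier anovulatory cycle, which may be small.

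4. **The article is condensed.** The full protocol may cap or record prior cycles, and Follow up says that the case record form registers fertility treatments. It therefore cannot be said that prior CC cycles go unrecorded. This objection stands for the recording. It does not remove the inconsistency, because the article states both the limit and the rules that allow it to be passed.

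**Conclusion.** The point holds in a limited form. The Background limit is not carried into the entry and treatment rules, and the units differ. A woman with k earlier anovulatory CC cycles can reach 12 + k CC treatment cycles, that is 13 at k = 1 and 14 at k = 2, if she is in a CC arm, not pregnant and still in treatment within eight months.

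This rests on three things: reading the limit as it is worded, in treatment cycles; reading the entry rule as exactly six ovulatory cycles; and the existence of eligible women with k of 1 or more. The Exclusion criteria and the 50 to 150 mg range make such women plausible but do not count them. The document shows that exceeding the limit is permitted, not that it happens or how often. Because the matter is one of safety and is cheap to settle, it should be reconciled.

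**What to change.** Reconcile the Background, Inclusion criteria, Study management, Interventions and Primary outcome measure sections:

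1. State whether the 12-cycle limit counts all CC treatment cycles or only ovulatory ones.
2. Make eligibility and the permitted CC cycles after randomisation consistent with that statement.
3. Ensure that the total number of prior CC cycles, ovulatory or not, is available at randomisation. If the case record form already holds it, nothing needs adding.

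Which limit or count applies is for the investigators and the ethics committee to decide.

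The cost is a short amendment and possibly one record field taken from the medical history.

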### Exclusion criteria

We will not include women below 18 years, women with abnormal prolactin or thyroid-stimulating hormone values, women with intolerable symptoms when treated with CC like hot flashes affecting daily function, headaches, vision changes, or depression and women who remain anovulatory on CC 150 mg daily for five days, the so called CC-resistant women.

### Ethical considerations

Approval for this study was obtained from the Medical Ethical Committee of the Medical Spectrum Twente Enschede and from the Central Committee on Research involving Human Subjects (CCMO), The Netherlands. In women fulfilling the inclusion criteria, written informed consent is obtained before randomisation is carried out.

### Randomisation

Randomisation is performed by accessing a password protected central internet-based randomisation program and is stratified for hospital. The randomisation list is prepared by an independent statistician. A 2x2 factorial design will be used. This will create four groups:

1) CC plus intercourse

2) CC plus IUI

3) gonadotrophins plus intercourse

4) gonadotrophins plus IUI

### Study management

All women participating in the study will undergo a basic fertility work-up including a semen-analysis and endocrinological investigation to rule out hyperprolactinemia and uncorrected thyroid dysfunction. Ovulation is induced with CC. From the third or fifth day until the seventh or ninth day after spontaneous or progesterone induced menstruation women will take CC with a minimum of 50 mg to a maximum of 150 mg a day. During the first six treatment cycles women will undergo CAT, HSG, THL and/or DLS and TT to exclude double sided tubal occlusion.

Women are eligible for the study after six ovulatory cycles proven by a cycle length of less than 35 days, a biphasic basal temperature curve, midluteal progesterone (> 16 nmol/l), detection of LH surge or sonography, depending on the local protocol.

Women eligible for the study will be referred to a research nurse for counselling and randomisation.

### Interventions

Women are allocated to a treatment strategy consisting of six cycles of CC plus intercourse or six cycles of gonadotrophins plus intercourse or six cycles of CC plus IUI or six cycles of gonadotrophins plus IUI. Women are treated until a pregnancy occurs within a treatment time horizon of eight months resulting in the birth of a healthy child (Figure 1).

**Figure 1 F1:**
[figure not shown]
Flow chart M-OVIN study.

Ovulation induction, semen preparation and insemination regimens will be done according to hospital specific protocols. Ovulation induction with CC will be started on the third to fifth day of a spontaneous menstrual or progesterone induced bleed, in the same dosage as used in the last ovulatory cycle, with a minimum of 50 mg to a maximum of 150 mg daily, for five days. If ovulation does not occur, the dosage will be increased with steps of 50 mg with a maximum of 150 mg daily in the next cycles. As couples are assumed to have regular intercourse, no specific timing advice will be given. Only if couples have a history of sexual problems they are advised to have regular intercourse, at least three times a week. Ovulation will be documented according to local protocol with either a biphasic temperature curve, or a follicle with a diameter ≥16 mm ;on transvaginal ultrasonography. In case of ovulation women will continue taking the same dose of CC until an end point is reached.

Ovulation induction with gonadotrophins will be started at the second to fifth day of a spontaneous or progesterone induced menstrual bleed according to the established chronic low dose step up regimen. Transvaginal ultrasound will be performed on day three of the cycle or according to local protocol. Women will not be stimulated if they have ovarian cysts >25 mm in mean diameter. The starting dose will be 50 or 75 IU daily. The follicular growth is strictly monitored by transvaginal ultrasound. If more than three dominant follicles (≥18  mm) are present, the cycle will be cancelled. When at least one follicle with a diameter of ≥ 16 mm is present, ovulation is induced by the administration of 5000 IU or 10000 IU of human chorionic gonadotrophin (hCG) followed by timed intercourse.

In case of IUI, semen samples will be processed within one hour of ejaculation by density gradient centrifugation followed by washing with culture medium. Women will be inseminated 36 hours after hCG injection. IUI will be performed once per cycle.

